#### Health economic analysis

This analysis will take the form of a cost–utility analysis to compare the difference in total costs and health utility weighted outcomes between competing alternatives. Costs will be calculated from a societal perspective, and will include the costs of program delivery, costs of health system resource utilization, and patient–caregiver indirect costs. Health utility represents the preference that an individual places on a given state of health. Responses to the MCS and PCS scores of the SF-12 will be converted to utilities [89]. Utilities can be converted into quality-adjusted life years (QALYs) by multiplying the health state utility by the amount of time a person spends in that state. Expressing outcomes in terms of QALYs allows for the comparison of incremental effectiveness between competing alternatives where survival is not expected to differ, but there is an expected difference in QOL. Total cost and QALYs from each group will be compared to calculate the incremental costs and effectiveness of the intervention relative to usual care, which will be used to calculate incremental cost-effectiveness ratios. Decision uncertainty analysis will be conducted using non-parametric bootstrapping techniques, and cost and effectiveness differences will be used to produce cost-effectiveness acceptability curves. Statistical uncertainty will be plotted on the cost-effectiveness plane.

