### Sample size

Based on other studies [30, 40] and our data from the initial acceptability of *TEMPO* [26], it is assumed that 40% of dyads approached will be ineligible, 40% will refuse participation, 15% will not return their baseline survey, and 25% will be lost to follow-up. Accordingly, 260 dyads will need to be approached to reach the target sample size 40 dyads (20 per group) at the 3-month follow-up [41].

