### Data collection

Participants complete an eligibility screening checklist (T0) and two questionnaires: baseline (T1) and 3 months later (T2). Upon return of their T2 questionnaire, participants are then invited to participate in a dyadic, semi-structured exit interview to further assess acceptability. Data are also collected through the local recruitment logs (covering all steps up to consent), the overall study log (follow-up of enrolled and randomized dyads), and website tracker information.

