#### Follow-up (T2) questionnaire

All patients and their caregivers complete the follow-up questionnaire separately. Along with the same measures included in T1, the T2 questionnaire includes (a) a health services and community-based resources survey to monitor usual care and co-interventions, (b) a *TEMPO* use and acceptability questionnaire based on previous acceptability measures [27, 40, 85], and (c) The System Usability Scale (SUS) [86]. The answers to each item of the *TEMPO* use and acceptability questionnaire will be examined individually and mostly used to guide the exit interviews. The SUS consists of 10 items assessing the usability of a website. Participants rate aspects of the website design on a 5-point Likert scale (1 = strongly disagree to 5 = strongly agree).

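### Incremental QALYs are to come from a comparison of group QALYs with no provision for baseline utility, which makes the estimate needlessly imprecise

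*Protocol article*

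**What the plan says.** All references are to the protocol article.

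- **Utilities and QALYs (Health economic analysis).** "Responses to the MCS and PCS scores of the SF-12 will be converted to utilities". QALYs are then obtained by "multiplying the health state utility by the amount of time a person spends in that state".
- **Comparison (same section).** "Total cost and QALYs from each group will be compared to calculate the incremental costs and effectiveness of the intervention relative to usual care". The increments feed the cost-effectiveness ratios, the acceptability curves and the cost-effectiveness plane. "Decision uncertainty analysis will be conducted using non-parametric bootstrapping techniques". Neither baseline utility nor the unit to be resampled is mentioned.
- **Timing (Data collection; Follow-up (T2) questionnaire).** There are two questionnaires, at baseline and 3 months later. The second repeats the SF-12: "Along with the same measures included in T1". Utility can therefore be derived at both times.
- **Size (Sample size).** "260 dyads will need to be approached to reach the target sample size 40 dyads (20 per group) at the 3-month follow-up".
- **Randomisation (Allocation and randomization).** Dyads are randomised 1:1, stratified by the higher HADS-Anxiety score in the dyad and by nothing else.
- **Baseline rule (Clinical significance).** Imbalance is examined for each outcome score. If the groups are imbalanced, a regression with the baseline score as covariate is used. The rule is conditional, gives no threshold, and does not mention QALYs or utilities.

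**The concern.** In a two-point QALY, baseline utility is part of the outcome itself. A chance difference between the arms at the start therefore enters the incremental QALYs twice: directly through u0, and again through its correlation with u1. Over only 3 months and with few dyads, that contribution can exceed a plausible treatment effect.

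The rule under Clinical significance does not close the gap. It covers outcome scores, and a QALY has no baseline score of its own. Even if it were borrowed, it acts only when imbalance is judged to be present. The imbalance that matters here is far smaller than one a conventional check would flag.

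The incremental QALYs, the ratio and the acceptability curve could then be noisier than the data require. The Discussion says the pilot's results will feed the design of a larger trial, so avoidable noise would be carried forward with them.

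**Working it through.** **Plan's own figures.** The article gives no utility SD, no correlation and no precision for the economic analysis, so there is no economic figure to reproduce. Its sample-size statement supplies 20 per arm. The stated losses ("40% of dyads approached will be ineligible, 40% will refuse participation, 15% will not return their baseline survey, and 25% will be lost to follow-up") give 40/(0.60 × 0.60 × 0.85 × 0.75) = 40/0.2295 = 174.3, i.e. 175 dyads, not 260. That is a separate matter. The main calculation uses the stated 20 per arm, with a sensitivity check below.

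**Inputs**
- From the article: n = 20 dyads per arm; horizon 0.25 year; utilities at two times; 0.2 SD as the effect of interest (the article's effect-size threshold for QOL and anxiety, applied here to utility at 3 months).
- Assumed: area-under-the-curve QALY by the trapezoid; one utility per dyad; equal SD at both times; baseline to follow-up correlation r from 0.3 to 0.8.

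Results are in units of the utility SD, so no value for that SD is needed.

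**Step 1: QALY.** 0.25 × (u0 + u1)/2 = 0.125 × (u0 + u1). A true effect of 0.2 SD at 3 months is worth 0.125 × 0.2 = 0.025 SD-years.

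**Step 2: variance of the arm difference**
- Unadjusted: 0.125² × (2/n) × (2 + 2r) × SD²
- Adjusted for u0: 0.125² × (2/n) × (1 − r²) × SD²
- Share of the unadjusted variance due to baseline: (1 + r)²/(2 + 2r) = (1 + r)/2, i.e. 65% at r = 0.3, 80% at 0.6 and 85% at 0.7
- Ratio of adjusted to unadjusted SE: √((1 − r)/2), i.e. 0.50 at r = 0.5 and 0.39 at r = 0.7

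**Step 3: probability of the wrong sign**, 1 − Φ(effect/SE), n = 20 per arm, true effect 0.2 SD

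| r | Unadjusted SE (SD-years) | Adjusted SE (SD-years) | Wrong sign, unadjusted | Wrong sign, adjusted |
|---|---|---|---|---|
| 0.3 | 0.0637 | 0.0377 | 34.7% | 25.4% |
| 0.6 | 0.0707 | 0.0316 | 36.2% | 21.5% |
| 0.8 | 0.0750 | 0.0237 | 36.9% | 14.6% |

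A simulation of 20,000 trials per value of r gave 34.7%, 36.2% and 36.5% unadjusted, and 25.6%, 21.6% and 14.8% adjusted. For a true effect of 0.5 SD, the formula gives 16–20% unadjusted and 5% down to 0.4% adjusted.

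**Step 4: how small an imbalance matters.** The SE of the baseline difference is √(2/20) = 0.316 SD. An adverse difference of 0.2/(1 + r) cancels the 0.2 SD effect in expectation, which is 0.125 SD at r = 0.6. A baseline difference at least that adverse has probability 35%. A 5% significance check would flag only about 2.02 × 0.316 = 0.64 SD.

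**Step 5: sensitivity**
- *Larger sample.* Approaching 260 dyads with the stated losses leaves 260 × 0.2295 ≈ 60, or 30 per arm. At r = 0.6 the SEs in SD units are √((2/30) × 3.2) = 0.462 and √((2/30) × 0.64) = 0.207, giving a wrong sign in 33% unadjusted and 17% adjusted.
- *Patients and caregivers pooled* as 40 independent people per arm, which is optimistic: 29–32% against 7–17%.
- *QALY from 3-month utility alone*, 0.25 × u1: the unadjusted risk is 1 − Φ(0.2/0.316) = 26%. The adjusted figures are those in the table. The gain is smaller, and slight at r = 0.3.

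**The case against.** The strongest reply is that this is one paragraph of a condensed article. It does not describe the QALYs as raw and does not exclude adjustment. A regression-adjusted increment is also a comparison of the groups, and a fuller economic plan may specify one. That stands as far as it goes: a reader might infer that the sponsor has committed to an unadjusted analysis, and the text does not support that. What remains is that the article describes how the increments are formed without a baseline term, while stating a baseline covariate rule for other outcomes in the preceding section.

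Three further inferences are tempting and not supported:

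- **That the result would be biased.** Under randomisation the unadjusted difference is unbiased. It is off only conditional on the imbalance that occurs, so the loss is one of precision.
- **That adjustment would make the sign trustworthy.** At 0.2 SD it is still wrong in 15–25% of trials. The planned bootstrap and acceptability curve would display that uncertainty, though centred on whichever estimate is used.
- **That individuals will be resampled.** The article names no bootstrap unit, and resampling dyads is compatible with it. On its own this is only missing detail.

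Two other points also stand. Stratifying on HADS-Anxiety should partly balance the mental-health part of utility, and the calculation gives no credit for that, although it does not balance physical health. The economic analysis appears neither among the objectives nor among the criteria for a larger trial, and no progression decision rests on it.

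**Conclusion.** The point holds in a limited form. As described, incremental QALYs come from group QALYs with no provision for baseline utility, and the nearby covariate rule is conditional and does not reach them. The cost is avoidable imprecision: the unadjusted SE is roughly 2 to 2.6 times the adjusted one for r = 0.5–0.7 (1/0.50 to 1/0.39).

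These sizes rest on the trapezoidal QALY, one utility per dyad, equal SDs and an assumed correlation, none of which the article gives. They do not depend on the utility SD. The wrong-sign comparison also depends on the size of the true effect. Because the analysis is exploratory and secondary, this is an inexpensive improvement and not a threat to the pilot's main conclusions.

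**What to change.** Add to Health economic analysis that:

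1. incremental QALYs will be estimated by regression on arm and baseline (T1) SF-12 utility, with the HADS-Anxiety stratum as a further covariate, regardless of any imbalance observed;
2. QALYs are calculated as the area under the curve between baseline and 3 months, if that is the intention;
3. the bootstrap resamples whole dyads within arm, because dyads are randomised, and refits the regression in each resample, with the cost-effectiveness plane and acceptability curve built from those fits.

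The cost is a sentence or two and a few lines of analysis code. No new data are needed, since the SF-12 is already collected at both times.

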#### Analysis of exit interview data

Exit interview transcripts will be analyzed in QSR NVivo using thematic analysis [90]. Initially, words or statements related to feasibility and acceptability will be extracted from the transcripts by assigning a code. Comparison of codes across transcripts will identify similarities and differences, which will lead to the identification of themes. Transcripts will be coded independently by two RAs to enhance credibility [91].

### Adverse event and protocol deviation reporting

Any serious adverse event occurring to a research participant will be reported to the lead research ethics committee without delay. Any protocol deviations will be recorded and depending on the nature, will be submitted to the ethics committee as an amendment.

## Discussion

Caregivers of men with prostate cancer remain a vulnerable group throughout the illness trajectory, as they often experience more anxiety and needs than patients [3, 6], but have access to fewer services [11]. This means that they are at high risk for both physical and emotional problems [1–3, 5, 6]. Despite some advocacy efforts, cancer care resources are already too stretched to respond to caregivers’ growing support needs. In support, a recent review of the costs of informal cancer care provision estimates that caregivers provide nearly $5,000 worth of care per month [4]. Although this significantly alleviates the demands on the healthcare system [4], it leaves caregivers particularly vulnerable to poor health outcomes. Thus, it is evident that there is a critical demand for studies testing the effectiveness and sustainability of interventions aimed at preserving and/or improving caregivers’ QOL. Pilot findings will not only be published, but will also be communicated to participants as a newsletter and/or a short video.

Although the number of web-based, self-management interventions is increasing [92], many fail to incorporate a dyadic approach to treatment and/or lack self-management strategies such as PA to target caregivers’ physical health [13, 14, 25]. Thus, *TEMPO* attempts to address these shortcomings. The present study primarily aims to test the feasibility and acceptability of *TEMPO* among men with prostate cancer and their caregivers. We posit that by targeting multiple risk factors of caregiver burden [5, 6], and combining the best evidence in terms of coping skills, PA training, and self-management, *TEMPO* has a great potential impact on clinical outcomes. In addition, the design and evaluation of this pilot trial was informed by the Medical Research Council’s (MRC) framework for complex interventions [93, 94], and is based on extensive prior development work, including the engagement of key stakeholders [26].

The proposed study protocol has some limitations. Notably, recruitment and participation is occurring during the novel COVID-19 pandemic, lending to specific challenges including the following: (a) recruitment may be delayed due to lack of identification of eligible dyads by hospitals, (b) eligible dyads may be those who are healthier and/or perceive themselves at lower risk of contracting the novel virus (and thus are more willing to participate), (c) participants may be limited in the extent/variety of their PA activities due to confinement measures, and (d) measures such as the HADS-Anxiety, HADS-Depression, PSS, and those pertaining to exercise intensity and self-efficacy may be artificially inflated or decreased as a result of the pandemic restrictions. Additional limitations include potential selection biases identified during the initial *TEMPO* acceptability study [26], namely participating dyads tended to be who are retired, and capable of engaging in medium to high intensity PA, and those who reported supportive dyadic relationships. A number of mitigation strategies have been considered and are being employed to address these challenges. The research team has developed, in consultation with the ethics committee, a comprehensive online recruitment strategy, including an online consent form. Additional suggestions for home-based activities and exercises have been added to the *TEMPO* health library, to reduce emphasis on activities undertaken outside of the home. The RAs who provide interface support to *TEMPO* participants have been informed of additional community-based resources that the dyads might benefit from during the pandemic. The semi-structured exit interviews contain questions that intend to tap into the pandemic-related limitations experienced by dyads to contextualize quantitative results.

In conclusion, our feasibility and acceptability analyses will begin to develop the knowledge base on *TEMPO*’s value for men with prostate cancer and their caregivers. Furthermore, the results will directly contribute to the design of a larger trial. Additionally, it lays the foundation on which future research can examine the impacts of web-based psychosocial and PA self-management programs among other dyadic populations coping with illnesses along a care continuum.

## Data Availability

Most of the data generated or analyzed during this study are included in this published article (and its supplementary information files). For any additional datasets used and/or analyzed during the current study, they are available from the corresponding author on reasonable request.

## Abbreviations

DCI: Dyadic Coping Inventory
ES: Effect size
HADS: Hospital Anxiety and Depression Scale
heiQ: Health Education Impact Questionnaire
HCP: Healthcare provider
HLQ: Health Literacy Questionnaire
IPAQ-SF: International Physical Activity Questionnaire-Short Form
MCS: Mental Component Summary (of the MOS SF-12)
MOS SF-12: Medical Outcome Survey Short-Form-12
MRC: Medical Research Council
MSES: Multidimensional Self-Efficacy for Exercise Scale
MUHC: McGill University Health Centre
PA: Physical activity
PCC: Prostate Cancer Canada
PCS: Physical Component Summary (of the MOS SF-12)
PSS: Perceived Stress Scale
PID: Participant identifier
QALYs: Quality-adjusted life years
QOL: Quality of life
RA: Research assistant
RDAS: Revised Dyadic Adjustment Scale
REB: Review Ethics Board
SHSC: Sunnybrook Health Sciences Centre
SUS: System Usability Scale
TBCC: Tom Baker Cancer Centre
*TEMPO*: Tailored, wEb-based, psychosocial and PA self-Management PrOgram
US: United States
VGH: Vancouver General Hospital
